### Sample size

The estimations of the sample size and power of our study are made based on diverse observations from acute-cold exposure studies in humans, and taking assumptions extrapolated from animal models [8, 13, 42]. We used a conservative approach to sample size estimation and assumed a relatively large standard deviation based on the heterogeneity of data published in humans. Moreover, due to the nature and duration of the study as well as the complexity of the outcomes to be measured, there were conservative estimates of effect sizes, accounting for higher drop-outs than that achieved in prior exercise-based RCTs. Power calculations are made for the primary outcome measures of BAT activity and mass.

It has been estimated that 50 g of activated BAT translates to  $\approx 5\%$  of REE in humans [8, 42]. An example of an ACTIBATE participant would be a sedentary man aged 19 years, body weight 90 kg, height 1.75m, and a body mass index of  $29.4 \text{ kg/m}^2$ , with a REE of  $\approx 2000 \text{ kcal/day}$ . We anticipated increases of 10% and 20% on activated BAT mass at 6 months in moderate-intensity and vigorous-intensity exercise groups, respectively, from a baseline level of 50 g, and change score SD of 50 g. This increase could translate into a REE of 110-120 kcal/day. Affecting energy balance by 50-100 kcal/day could prevent weight gain in the vast majority of the population [43]. Assuming a bilateral alternative (which means that an effect in either direction will be interpreted), we can detect differences of at least 10% in BAT mass with a power of  $>80\%$  and  $\alpha$  of 0.05 in a group of 17 participants. With this number of participants per group we can also detect differences of 10-20% in BAT activity with a power of  $>80\%$  and  $\alpha$  of 0.05. Since several studies reported sex-differences in BAT mass [9], all the analysis will be conducted in men and women separately. Therefore, to avoid loss of statistical power, a total of 34 (50% women) participants should be enrolled in each group. Assuming a maximum loss at follow-up of 30%, we decided to recruit 50 participants (50% women) for each of the study groups: control, moderate-intensity and vigorous-intensity groups. A total of 150 participants (of which 75 will be women and 75 men) will be enrolled in ACTIBATE. We believe this sample size is feasible and realistic based on our previous experiences in RCTs [44, 45]. We used IBM-SPSS Sample power software (version 3.0.1) for calculations.

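### At the printed change-score SD of 50 g, 17 per group gives about 6% power for a 10% difference in BAT mass (about 9% for 20%), not the stated more than 80%.

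*Protocol*

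**What the plan says.** BAT activity and mass are the primary outcomes, and the Sample size section says that the power calculations are made for them. It describes its method in these terms: "We used a conservative approach to sample size estimation and assumed a relatively large standard deviation".

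The expected effects come first: "We anticipated increases of 10% and 20% on activated BAT mass at 6 months in moderate-intensity and vigorous-intensity exercise groups". The starting value and the spread to which these percentages apply are then set out: "from a baseline level of 50 g, and change score SD of 50 g". With a two-sided alternative, the section concludes that "we can detect differences of at least 10% in BAT mass with a power of" more than 80%, for 17 participants per group and an alpha of 0.05. It adds that the same number per group gives more than 80% power for differences of 10-20% in BAT activity.

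Every later number is built on the 17. Because men and women are to be analysed separately, it is doubled: "a total of 34 (50% women) participants should be enrolled in each group". Attrition is then added: "Assuming a maximum loss at follow-up of 30%, we decided to recruit 50 participants (50% women) for each of the study groups". Three groups of 50 make 150.

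**The concern.** The anticipated effects are one tenth and one fifth of the stated SD. Seventeen per group suits a difference of about one full SD. The stated power and the stated inputs therefore describe different trials.

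This is the only power statement for the primary outcome that can be checked, and the size of the trial follows from it. If the SD of 50 g is right, the trial has almost no chance of detecting the effects it expects. A reader who trusted the claim could take a non-significant result as evidence against a 10% effect, although the confidence interval would include effects several times larger.

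**Working it through.** **Inputs, all from the Sample size section.** Baseline 50 g; increases of 10% and 20%; change-score SD 50 g; two-sided alpha 0.05; 17 per group. No control-group change is given, so it is taken as 0 (assumption).

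**Percentages in grams.** 0.10 × 50 = 5 g and 0.20 × 50 = 10 g. The section's energy figures agree: 50 g is put at about 5% of a resting expenditure of 2000 kcal/day, which is 100 kcal/day, so 55-60 g corresponds to the 110-120 kcal/day it quotes.

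**Which test.** BAT is measured at baseline and week 25 only (Table 2). The time × group interaction in the Statistical analysis section therefore amounts to comparing change scores between groups, and the two-sample t-test is the matching calculation.

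**Does the stated figure reproduce?** Standardised effects: d = 5/50 = 0.1 and 10/50 = 0.2. Noncentrality is d × √(n/2): 0.1 × √8.5 = 0.29 and 0.2 × √8.5 = 0.58, against a critical t of about 2.04 on 32 degrees of freedom. Power is **5.9%** and **8.7%**. The stated figure of more than 80% does not reproduce.

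**What 17 per group can detect at SD 50 g.** Eighty percent power needs d = 0.991, and 0.991 × 50 = **49.6 g**, or 99% of baseline. The 95% CI half-width is about 2.04 × 50 × √(2/17) = **35 g**, or 70% of baseline.

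**Number needed for 80% power.** The normal approximation 2 × (1.96 + 0.84)² / d² gives 1,570 per group for 5 g and 393 for 10 g. The exact t calculation gives **1,571** and **394**.

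**Other readings, SD 50 g unless noted.**

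| Reading | Power, 5 g | Power, 10 g |
|---|---|---|
| Two-sample, two-sided, 17 per group | 5.9% | 8.7% |
| Two-sample, one-sided, 17 per group | 8.7% | 14.1% |
| Within-group paired, two-sided, n = 17 | 6.7% | 12.1% |
| Two-sample, sexes pooled, 34 per group | 6.9% | 12.8% |
| Two-sample, pooled with no loss, 50 per group | 7.9% | 16.8% |
| Two-sample, 50 read as a variance (SD 7.07 g), 17 per group | 51.6% | 97.9% |

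A three-group ANOVA with mean changes of 0, 5 and 10 g and 17 per group has 7.5% power. With 50 read as a variance, even a paired test reaches only 78.1% for 5 g. No reading tried at an SD of 50 g comes near 80%, and the variance reading still falls short for the 10% difference that the claim names.

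**What does reproduce 17.** With d = 1.0, power is 80.7% at 17 per group and 78.1% at 16, so 17 is exactly the answer for a difference of one SD. For a 5 g difference the SD would have to be 5/0.991 = **5.05 g**. A paired test would need about 6.9 g.

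**Later steps.** 17 × 2 = 34, and 34/(1 − 0.30) = 48.6, which rounds up to 49 and was set at 50. These steps are sound; the error lies in the first figure.

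**The case against.** The strongest reply is that the power may be right and the SD misprinted. An SD of 5 g gives exactly 17 per group, which fits a typing slip or a calculation run with another SD as well as it fits a wrong power figure. That stands: the document does not settle which number is at fault. It does not clear the text, though. An SD of 5 g is 10% of the baseline mean, which is hard to square with a conservative, relatively large SD based on heterogeneous human data.

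The section also makes a power claim for BAT activity and cites feasibility. The BAT-mass calculation is therefore not the only support offered for 150. But the activity claim has no SD and cannot be checked, and feasibility says nothing about power.

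The protocol sets no rule for interpreting a null result, so the risk of misreading one is an inference, not something the plan states. That is fair.

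The pooled-sex and paired figures describe analyses other than the planned ones. That is also fair: they are given only to show that no generous reading rescues the claim.

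Covariate adjustment might be invoked. To reach 80% at 17 per group for 5 g, covariates would have to cut the SD from 50 g to 5.05 g, that is, explain 1 − (5.05/50)² = 99% of the change-score variance. That is not credible.

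**Conclusion.** The stated power is wrong on the protocol's own inputs. At a change-score SD of 50 g, 17 per group has 5.9% power for the 10% effect and 8.7% for the 20% effect, and the detectable difference is about ten times the 5 g claimed. This assumes no change in the control group and a comparison of change scores at two-sided 0.05. The multiplicity adjustment named in the Statistical analysis section (Holm's procedure) would lower power further. The conclusion is conditional on the printed SD: the SD, the effect, the group size and the power cannot all hold, and the sponsor must say which one gives way. Until then, the 150 participants have no checkable power support for the primary outcome.

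**What to change.** Reconcile the SD with the power claim and rewrite the paragraph.

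- **If another SD was used:** state it with its source, remove the 50 g, and revise the description of the SD as relatively large if it no longer fits.
- **If 50 g stands:** replace the claim with wording such as: *With a change-score SD of 50 g, 17 per group gives 80% power for a difference of about 50 g (about 100% of baseline); power for differences of 10% and 20% is about 6% and 9%.* If a pooled figure is added (34 per group, detectable difference about 34 g), label it as outside the planned sex-specific analysis. Then give a different rationale for 150, such as feasibility or the precision achievable, or restate what the trial can show.
- **BAT activity:** give the SD behind the 10-20% claim, or delete it.
- **Interpretation:** state that a non-significant result does not exclude effects of the anticipated size.

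The cost is a rewritten Sample size section. The correction itself adds no participants and changes no procedures. If 50 g stands, the price is a much less favourable power statement and the need to defend the sample size on other grounds.

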### Statistical analysis

All outcome variables will be checked for normality and results will be expressed as mean and SD or median and ranges. For between group comparisons at baseline (control group vs moderate-intensity and vigorous-intensity), we will analyse continuous variables with one-way analysis of variance or the non-parametric method of Kruskal-Wallis, and Chi-square tests (or exact techniques if needed), as appropriate. We will use General Lineal Models to assess the training effects (time  $\times$  group interactions) on the primary and secondary study outcomes. We will adjust multiple comparisons for mass significance [46]. We will also examine the differences between drop-outs and participants who remain in the study. We will analyse the data according to the intention-to-treat principle [47], and will handle missing data due to drop-outs or non-compliance using multiple imputation methods. To fully appreciate the potential

influence of missing responses, we will perform sensitivity analysis. In addition, multiple regression analysis will be performed to evaluate potential independent predictors of BAT activity.

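### Running every analysis separately by sex leaves no overall answer to the primary objective and no planned sex-by-group contrast; one model with sex as a factor should be primary

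*Protocol*

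**What the plan says.** Under Sample size, the Protocol justifies separation by sex with published sex differences in BAT mass and concludes that "all the analysis will be conducted in men and women separately". The power statement is made for a comparison "in a group of 17 participants". That number is then doubled to 34 per group, half of them women, expressly to protect power under the split, and raised to 50 per group for a loss of up to 30%. The planning values are given as "We anticipated increases of 10% and 20% on activated BAT mass at 6 months in moderate-intensity and vigorous-intensity exercise groups", "from a baseline level of 50 g, and change score SD of 50 g".

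Under Statistical analysis, the Protocol says "We will use General Lineal Models to assess the training effects", expressed as time-by-group interactions, and commits to a multiplicity adjustment citing Holm's procedure. That section does not repeat the split. It names no sex term, no sex-by-group interaction and no pooled analysis.

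The primary objective, at the end of Background, is the dose-effect of exercise intensity on BAT activity and mass in young adults. It is not framed as one question for men and another for women.

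**The concern.** The reason does not support the rule. If men and women carry different amounts of BAT, a sex term and the baseline value in the model deal with that. Separate analyses would be called for only if the training effect were expected to differ by sex, and the Protocol cites nothing to that effect.

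Three consequences follow from the wording:

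- There will be two answers to a question asked once, with no rule for combining them if they disagree.
- No contrast between the sexes is planned. A reader who sees significance in one sex only has nothing in the plan that shows whether the effects differ.
- Each comparison is tested twice on half the available participants, although all of them are enrolled, trained and scanned anyway.

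**Working it through.** **Inputs** (Protocol, Sample size): baseline 50 g; change-score SD 50 g; anticipated increases 10% (5 g) and 20% (10 g); two-sided alpha 0.05; 17 completers per sex per group; 30% loss. No change is given for controls, so 0 g is assumed. SD 50 g is taken to apply within each sex. No baseline-to-follow-up correlation is given, so no gain from baseline adjustment is counted.

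**1. The plan's own figures.** The later steps reproduce: 17 × 2 = 34 per group; 17 / 0.7 = 24.3, so 25 per sex and 50 per group; 3 × 50 = 150. The starting figure does not. For 5 g, the noncentrality is 5 / (50 × √(2/17)) = 5 / 17.1 = 0.29, and the two-sample t-test has 5.9% power, not more than 80%. Seventeen per group gives 80.7% only for a difference of one SD, that is 50 g.

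**2. Standard error of a group difference.** SE = SD × √(2/n).
- One sex: 50 × √(2/17) = 17.1 g.
- Pooled, with sex in the model: 50 × √(2/34) = 12.1 g, smaller by a factor of √2.

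**3. Difference detectable with 80% power** (noncentral t).
- 17 per arm: 0.991 SD × 50 = 49.6 g.
- 34 per arm: 0.690 SD × 50 = 34.5 g, about 30% smaller.

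**4. Power for an effect common to both sexes.** The pooled column uses six cells of 17 with 102 − 6 = 96 residual degrees of freedom.

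| True difference | One sex, 17 vs 17 | Pooled, 34 vs 34 |
|---|---|---|
| 5 g | 5.9% | 6.9% |
| 10 g | 8.7% | 12.9% |
| 50 g | 80.7% | 98.3% |

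**5. Sex-by-group interaction.** SE = 50 × √(4/17) = 24.3 g. The interaction detectable with 80% power is (1.96 + 0.84) × 24.3 ≈ 68 g. Power is 53% for a 50 g interaction and 5% to 7% for one of 5 g to 10 g.

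**6. Discordant results under an identical effect.** With power p in each sex, the chance that exactly one sex is significant is 2p(1 − p).
- p = 0.80: 2 × 0.80 × 0.20 = 32%.
- p = 0.807: 2 × 0.807 × 0.193 = 31%.
- At the anticipated effects: 2 × 0.059 × 0.941 = 11% for 5 g and 2 × 0.087 × 0.913 = 16% for 10 g.

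**7. False positives for one contrast tested in both sexes.** With no adjustment across sexes, 1 − 0.95² = 9.75%. The Protocol promises an adjustment but does not say whether the two sexes form one family. That detail may sit in a statistical analysis plan that was not available, so this is the size of the risk if they do not, not a finding in itself.

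**The case against.** The strongest reply is that the split was declared in advance and paid for. A reader might infer that it halves the sample and causes an unplanned loss of power. The documents do not support that: the comparison within one sex is the one the trial was sized for, and the group size was doubled for that purpose. What remains is that a more precise analysis of the same participants is ruled out.

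A reader might also infer that the design makes a sex difference untestable. It does not. Two independent estimates with standard errors can be subtracted and tested. The accurate statement is that no such comparison is planned. Nor does the Protocol say that a sex difference would be claimed from significance in one sex alone; the 31% to 32% describes a risk in reading the results, not a planned inference. An explicit interaction test would itself be weak.

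Stratifying can be defended on two technical grounds. If the effect is a percentage of baseline and baseline differs by sex, the gram changes differ by sex even when the percentage is the same. The residual variance may differ too. Both points are fair, but neither requires separate analyses. A group-by-sex term with sex-specific estimates from one model covers the first, and a model allowing sex-specific variances covers the second.

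Finally, covariates and interaction terms are often left to a statistical analysis plan. Here the Protocol's rule covers every analysis, so a plan that made a pooled analysis primary would contradict it.

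**Conclusion.** The concern holds as a matter of analysis choice. As worded, the Protocol provides no single estimate for its primary objective and no sex-by-group contrast, on the strength of a reason that concerns level and not response. The cost in precision is a standard error of 17.1 g where 12.1 g is available, and a detectable difference of 49.6 g where 34.5 g is available. These figures assume SD 50 g in both sexes, 17 completers per sex per arm and a broadly common effect.

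It would be wrong to conclude that pooling repairs the sample size. At the anticipated 5 g and 10 g, with no change in controls, power moves only from about 6% to 7% and from about 9% to 13%. Even the pooled detectable difference of 34.5 g is about 3.5 to 7 times what the Protocol expects. The mismatch between effect size, SD and claimed power is a separate defect in the same section. The change is worth making, but it is not what decides whether the trial is adequately powered.

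**What to change.** Replace the sentence under Sample size, and add to Statistical analysis, wording such as:

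*The primary analysis compares groups in all randomised participants in one model with group, sex and baseline BAT. The group-by-sex interaction and sex-specific estimates with confidence intervals are reported as secondary.*

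State alongside it that the interaction has low power (about 68 g is needed for 80% at SD 50 g), so that a non-significant result is not read as evidence of equal effects. If unequal variances by sex are expected, allow for them in the same model.

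Restate the power for the pooled comparison with 34 to 35 evaluable per group (50 × 0.7 = 35). Separately, reconcile the effect size, SD and power claim, which do not agree under either analysis.

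The cost is a change of wording: no further participants, scans or visits. The downside is that the by-sex results, which the Protocol now treats as the main analysis, become secondary.

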### Statistical analysis

All outcome variables will be checked for normality and results will be expressed as mean and SD or median and ranges. For between group comparisons at baseline (control group vs moderate-intensity and vigorous-intensity), we will analyse continuous variables with one-way analysis of variance or the non-parametric method of Kruskal-Wallis, and Chi-square tests (or exact techniques if needed), as appropriate. We will use General Lineal Models to assess the training effects (time  $\times$  group interactions) on the primary and secondary study outcomes. We will adjust multiple comparisons for mass significance [46]. We will also examine the differences between drop-outs and participants who remain in the study. We will analyse the data according to the intention-to-treat principle [47], and will handle missing data due to drop-outs or non-compliance using multiple imputation methods. To fully appreciate the potential

influence of missing responses, we will perform sensitivity analysis. In addition, multiple regression analysis will be performed to evaluate potential independent predictors of BAT activity.

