## ABSTRACT

**Aims:** The energy expenditure capacity of brown adipose tissue (BAT) makes it an attractive target as a therapy against obesity and type 2 diabetes. BAT activators namely catecholamines, natriuretic peptides and certain myokines, are secreted in response to exercise. ACTIBATE will determine the effect of exercise on BAT activity and mass measured by positron emission tomography/computed tomography (PET/CT, primary outcome) in young adults. ACTIBATE will also investigate the physiological consequences of activating BAT (secondary outcomes).

**Methods:** ACTIBATE will recruit 150 sedentary, healthy, young adults (50% women) aged 18-25 years. Eligible participants will be randomly assigned to a non-exercise group (n=50) or one of two exercise groups (n=50 each). Participants in the exercise groups will perform aerobic and strength training 3-4 days/week at a heart rate equivalent to 60% of heart rate reserve (HRres), and at 50% of 1 repetition maximum (RM) for the moderate-intensity group, and at 80% of HRres and 70%RM for the vigorous-intensity group. Laboratory measures completed at baseline and 6 months include BAT activity and mass, resting energy expenditure, meal and cold-induced thermogenesis, body temperature regulation and shivering threshold, body composition and cardiovascular disease risk factors. We will also obtain biopsies from abdominal subcutaneous white adipose tissue and skeletal muscle to analyse the expression of genes encoding proteins involved in the thermogenic machinery.

**Discussion:** ACTIBATE will allow quantification of the dose-response of different exercise intensities (i.e. no exercise, moderate-intensity and vigorous-intensity) BAT activity and mass in humans. Findings from ACTIBATE will have significant implications for our understanding of exercise and its protective effects against the development of type 2 diabetes, obesity and related metabolic diseases.

ClinicalTrials.gov ID: NCT02365129

**Key words:** Brown adipose tissue; energy metabolism; thermogenesis; body temperature regulation; obesity; type 2 diabetes.

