A potential clinical implication of activating BAT relates to the stimulation of resting energy expenditure (REE), meal-induced thermogenesis (MIT) [13] and cold-induced thermogenesis (CIT) [14]. In humans, MIT seems to be higher in those possessing BAT, so that they convert a higher proportion of the calories in the meal directly to heat than do individuals without brown fat [15]. CIT has been strongly correlated with BAT, and it has been estimated that BAT increases total energy expenditure on 200-400 kcal/day when humans are under cold conditions [16]. In addition, it has been proposed that even if BAT activation would not produce enough energy expenditure to induce a negative energy balance, it could exert metabolic benefits on the prevention and treatment of type 2 diabetes and associated dyslipidaemia [17-19].

The SNS, through adrenergic signalling, is the classical regulator of BAT; however, recent findings have shown a pool of novel BAT activators that sidestep the need for stimulating the SNS, such as cardiac natriuretic peptides [20], irisin [21],  $\beta$ -aminoisobutyric acid (BAIBA) [22], interleukin-6 (IL-6) [23], and fibroblast growth factor 21 [24]. Of interest is that both SNS and non-SNS BAT activators are sensitive to exercise, which opens new horizons to study the potential effect of exercise-based therapeutic interventions [25, 26]. Several studies conducted in animal models have reported an increased BAT activity and browning after an exercise-based intervention [21, 27-30], yet there is still some controversy [31-35]. In humans, there seem to exist a positive association of exercise with BAT and browning activity [36-38].

The primary objective of the ACTIBATE randomized controlled trial (RCT) is to quantify the dose-effect of different exercise intensities (i.e. no exercise, moderate-intensity and vigorous-intensity), on BAT activity and mass (primary outcome), and on REE, MIT, CIT, body temperature regulation and shivering threshold, body composition and cardiovascular

disease risk factors in young adults. We will also obtain biopsies from abdominal subcutaneous white adipose tissue and skeletal muscle to analyse the expression of genes encoding proteins involved in the thermogenic machinery.

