### Exercise program rationale and selection of doses

With the final aim of making the exercise program transferable to society, the basis for the specific exercise dose in ACTIBATE is the physical activity recommendations for adults proposed by the World Health Organization [48]. Since there is no information regarding the ideal exercise model to activate and recruit BAT, ACTIBATE will combine both aerobic and resistance training. A major objective of the study is to evaluate various exercise intensity levels (moderate and vigorous) that fall within the current public health recommendations to test whether higher intensity levels provide more benefit than the standard moderate-intensity level.

The length of the trial is 6 months based on results from previous large scale RCT, and based on the fact that substantial physiological adaptations occur within the first 3-6 months of exercise [49]. We have also considered the increased logistical and participation burdens, which indeed might lead to poorer adherence, as well as the cost of running a highly controlled-laboratory based study for a longer period. No dietary prescription or instructions will be provided to the participants in both control and exercise groups, except for the prescription to not change their dietary habits during the study period.

**Volume.** An important goal in the development of exercise doses of ACTIBATE was to keep the total volume (in minutes) of weekly exercise similar in both intervention groups while ensuring that the aerobic, as well as the resistance training, prescriptions met current guidelines [48, 50]. We will achieve both goals since the total time of aerobic exercise in both moderate-intensity and vigorous-intensity groups will be 150 minutes/week, whereas the time needed to complete the resistance training exercises will be  $\approx 80$  minutes for both groups.

It is estimated that 150 minutes/week of moderate-intensity [ $\approx 3$ -5.9 metabolic equivalents (METs), 1 MET= 3.5 ml O2/kg/min] aerobic physical activity is equivalent to 1000 kcal/week, which is associated with lower rates of cardiovascular disease and premature mortality [51]. An energy expenditure of 1000 kcal/week can also be achieved with  $\approx 75$  minutes/week of vigorous intensity ( $\geq 6$  METs).

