| 

-Age: 18-25 years.

-BMI: 18.5-35 kg/m^2.

-Not engaged in regular physical activity >20 min on >3 days/week.

-Not participating in a weight loss program.

-Stable weight over the last 3 months (body weight changes <3 kg).

-Normal electrocardiogram.

-Participants must be capable and willing to provide consent, understand exclusion criteria and accept the randomized group assignment.

 | 

- History of cardiovascular disease.

- Diabetes or hypertension.

- Pregnancy, or planning to get pregnant during the study period.

-Medication for hypertension, hyperlipidemia, hyperuricemia or other illness.

-Beta blockers or benzodiazepines use.

-Smoking.

-Frequent exposure to cold temperatures (Granada is surrounded by high mountains where people can ski or do trekking).

-Taking medication for thyroid.

-Other significant medical conditions that are life-threatening or that can interfere with or be aggravated by exercise.

- Unwillingness to either complete the study requirements or to be randomized into control or training group.

- A first-degree relative with history of cancer.

 |

**Table 2.** Summary of time point measurements of the primary and secondary outcomes of the study.

| Measurements                   | 1-
Baseline
(week 0) | 2-
Week
4 | 3-
Week
8 | 4-
Week
12 | 5-
Week
16 | 6-
Week
20 | 7-
Post-int
(week 25) |
|--------------------------------|----------------------------|-----------------|-----------------|------------------|------------------|------------------|-----------------------------|
| Primary outcome         |                            |                 |                 |                  |                  |                  |                             |
| BAT activity and mass          | x                          |                 |                 |                  |                  |                  | x                           |
| Secondary outcomes      |                            |                 |                 |                  |                  |                  |                             |

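### For BAT, the planned time × group test is a change-score analysis; adjusting for baseline BAT would be more precise, using data already collected

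*Protocol*

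**What the plan says.** The Statistical analysis section names the method for the primary and secondary outcomes: "We will use General Lineal Models to assess the training effects", with the training effect defined as the time × group interaction. It adds "We will adjust multiple comparisons for mass significance", citing the Holm procedure, but does not list the comparisons covered. It names no baseline covariate.

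BAT has two measurements. The Abstract says "Laboratory measures completed at baseline and 6 months include BAT activity and mass", and Table 2 marks the row "BAT activity and mass" at week 0 and week 25 only. Several other outcomes (for example resting energy expenditure, body composition, cardiorespiratory fitness and muscular strength) are marked at weeks 0, 8, 16 and 25.

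The primary objective (Background) "is to quantify the dose-effect of different exercise intensities". The section on exercise program rationale adds a second question, to "test whether higher intensity levels provide more benefit than the standard moderate-intensity level". The Sample size section says "We anticipated increases of 10% and 20% on activated BAT mass at 6 months in moderate-intensity and vigorous-intensity exercise groups", from a baseline of 50 g with a change-score SD of 50 g, and plans all analyses separately in men and women.

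**The concern.** With only two visits, the interaction carries no more information than each participant's change. A change score subtracts the whole baseline value, whatever the actual relation between baseline and follow-up. When the correlation r is below 1 and the variances are equal, that over-corrects and leaves avoidable noise in the group comparison. The assumed change SD is as large as the baseline mean, and only 17 completers are expected per arm within each sex, so there is little precision to spare. The baseline scan is already in the design, so using it as a covariate costs nothing in data collection.

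**Working it through.** **Inputs.** From the Sample size section: 17 completers per arm per sex (34 per arm in all), baseline 50 g, increases of 10% and 20% (5 g and 10 g), change SD 50 g, two-sided α = 0.05. Assumed, because the protocol does not state them: zero change in controls, equal variance at both visits, and r between 0.3 and 0.9.

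**1. The plan's own figure.** The protocol claims more than 80% power for a 10% difference with 17 per group. The standardised difference is 5/50 = 0.1. A two-sample t-test with 17 per group then has 5.9% power (8.7% for 10 g). By n = 2(1.96 + 0.84)²/d², 80% power needs about 1,570 per group for 5 g and 393 for 10 g. Seventeen fits only d ≈ 1 (power 80.7%), that is, an SD near 5 g. The claim does not reproduce. That is a separate and larger problem, but it limits what any change of model can achieve.

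**2. Equivalence.** With visits 0 and 1, the interaction compares the mean of Y1 − Y0 across arms. This is a one-way ANOVA of change with 2 numerator df and, at 17 per arm, 51 − 3 = 48 residual df. A numerical check gave the same F both ways (1.1216).

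**3. Variance.** Let σ² be the variance at each visit.
- Change score: 2σ²(1 − r).
- ANCOVA residual: σ²(1 − r²).
- Ratio: (1 − r²)/[2(1 − r)] = (1 + r)/2, below 1 for every r < 1, at the price of 1 df.

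This gives 0.75 at r = 0.5, 0.85 at 0.7 and 0.90 at 0.8. The sample-size equivalents are 1/0.75 = 1.33, 1/0.85 = 1.18 and 1/0.90 = 1.11.

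**4. Chance imbalance.** Given a baseline difference D between two arms, the expected change-score difference is the true effect minus (1 − r)D. At r = 0.5 a change SD of 50 g implies σ = 50/√(2 × 0.5) = 50 g, so the standard error of D with 17 per arm is 50 × √(2/17) = 17.1 g. An imbalance of one standard error shifts the estimate by 0.5 × 17.1 ≈ 8.6 g, close to the whole anticipated vigorous effect. Over repeated randomisations this averages to zero, so it is noise and not bias.

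**5. Power on the protocol's inputs.** For means 0/5/10 g the noncentrality is n × 50/variance, for example 17 × 50/2500 = 0.34 for change scores at 17 per arm.

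| Three-arm test | Variance ratio | 17 per arm | 34 per arm | n per arm for 80% |
|---|---|---|---|---|
| Change scores (as planned) | 1 | 7.5% | 10.3% | 483 |
| ANCOVA, r = 0.9 | 0.95 | 7.6% | 10.6% | 459 |
| ANCOVA, r = 0.7 | 0.85 | 7.9% | 11.3% | 411 |
| ANCOVA, r = 0.5 | 0.75 | 8.3% | 12.2% | 363 |
| ANCOVA, r = 0.3 | 0.65 | 8.9% | 13.4% | 315 |

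For vigorous versus control alone, using the three-arm error term and before any multiplicity adjustment, power at 17 per arm goes from 8.8% to between 9.0% (r = 0.9) and 10.9% (r = 0.3).

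**6. Sensitivity to the SD.** At an SD of 5 g the planned three-arm test already exceeds 99.9% at 17 per arm, so adjustment adds nothing. At an illustrative 10 g, vigorous versus control goes from 81.5% to 90.9% at r = 0.5.

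**7. An ordered contrast.** With equal arms, the contrast (−1, 0, +1) gives the moderate arm zero weight, so it is exactly vigorous minus control. At the n where the three-arm test has 80% power, the contrast has 87.4% for 0/5/10, 76.8% for a step (0/10/10 or 0/0/10), 34.2% for 0/10/5 and 5.0% for 0/10/0.

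**The case against.** The strongest defence is that nothing here is an error. A change-score comparison in a randomised trial is unbiased with correct type I error. A general linear model can take covariates, and covariates are commonly settled in the SAP, which was not available for this review. The value of r is unknown, and at the stated SD the power gain is only a point or so.

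Most of that stands, and it limits the point to an efficiency improvement. It does not remove it: the protocol does name its test, that test is a change-score analysis for BAT, and a more precise one is available from the same data.

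A reader might infer more, in four ways that the documents do not support:
- That the planned test is biased, or ignores the correlation between visits. The change-score variance depends on r; the test simply gives baseline a fixed weight that is generally not the best one.
- That the unordered three-arm test is the trial's only inference, so the dose question goes unanswered. Multiplicity-adjusted comparisons are also planned.
- That an ordered dose contrast would improve matters at no cost. It equals vigorous versus control, so it duplicates one pairwise comparison, does not address vigorous versus moderate, cannot tell a graded response from a step, and loses power if the response is not graded.
- That better modelling makes the sample size adequate. The table above shows otherwise.

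**Conclusion.** The point holds as a free improvement in precision for the primary outcome. Baseline adjustment reduces the residual variance to (1+r)/2 of the change-score variance, equivalent to roughly 11–33% more participants for r between 0.8 and 0.5. This rests on equal variances at the two visits and on values of r that the documents do not supply. At the protocol's own change SD of 50 g, power remains below 10% for the three-arm test at 17 per arm, so the sample-size justification has to be dealt with separately. Adding an ordered contrast is an optional trade-off and not part of the recommendation.

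**What to change.** Amend the Statistical analysis section so that the primary model for BAT is an ANCOVA of the week-25 value on group, with baseline BAT as covariate. Fit it within each sex, as the Sample size section plans; sex would enter as a covariate only in a pooled model. Follow it with the Holm-adjusted pairwise comparisons, naming them and including vigorous versus moderate.

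Use the same form for secondary outcomes measured only at baseline and week 25. For those measured at weeks 0, 8, 16 and 25, adjust for baseline in a repeated-measures model that keeps weeks 8 and 16; a simple week-25 ANCOVA would discard them.

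If an ordered contrast is wanted as well, state its place in the testing order and that it coincides with vigorous versus control.

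The cost is a change of wording and 1 df per primary model; no extra measurement is needed. Fix it before follow-up outcomes are seen by group, so that the choice of covariate cannot depend on the results. If the SAP already specifies baseline adjustment, the protocol need only be brought into line.
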